### Assessing clinical outcomes

The primary clinical outcome measure is the OASI rate which will be evaluated using patient-level data from the unit’s Maternity Information System (MIS).

#### Data source

Patient-level data will be extracted from local electronic MIS for 15 units in England, Wales and Scotland, and from the Scottish Morbidity Record 02 (SMR02) and Scottish Birth Record (SBR) for one unit in Scotland. MIS capture detailed demographic and clinical information related to maternity care and outcomes, with the data entered by midwives and support staff in the antenatal clinic or labour ward. Although the participating units use nine different systems and the data format could slightly differ, there is sufficient similarity between them to develop a single dataset for analysis. SMR02, submitted by maternity units to the Information Services Division Scotland since 1975, collects data for all women admitted as inpatients or day cases to Scottish maternity units [28]. This register is subjected to regular quality assurance checks and since the late 1970s has been more than 99% complete.

The pre-defined data specification for MIS, SMR02 and SBR includes perineal trauma, maternal characteristics (e.g. age, body mass index, parity) and intrapartum care (e.g. episiotomy, induction of labour, epidural use, shoulder dystocia and mode of birth). An 18-month extract of patient-level data (which will include a baseline, transition and implementation phase) will be extracted from the data sources. This will be obtained at the end of March or April 2018 depending on when the region began roll-out to ensure 18 months of data for all units. While data for a longer period for pre-rollout is available, we will follow the recommendation that primary analyses need to be based mainly on data from those exposed to the intervention or control while clusters are in both conditions, supplemented only by data from immediately before or after the roll-out period [29]. The dataset will not include any patient identifiable information. It will be transferred to and stored at a secure server, and only named individuals from the Project Team will have access to the dataset. All participating units have signed a Data Sharing Agreement with the RCOG, and all users of the data are obliged to fully comply with Data Protection Legislation.

#### Data management

Prior to analyses, the data from each unit will be cleaned and re-coded to ensure consistent definitions for all variables. For example, in some units’ MIS, the perineal trauma variable might also include degree of tears (e.g. 3a, 3b, 3c, 4) which will be coded as 1 if the perineal tear is either 3rd or 4th degree.

Data quality will be assessed by checking data completeness, plausible distributions and internal consistency. Data completeness is expected to be very high in the key data items such as birth trauma, mode of birth and birth weight, however, the completeness of other variables such as labour onset and epidural use might be variable across units [25]. Multiple imputation methods will be used to deal with missing data, if possible, following an assessment of the extent and patterns of missing data. Plausible distribution checks include assessing whether the distributions calculated from non-missing data is within a clinically possible and acceptable range (e.g. OASI rates less than 15%). Internal consistency checks include assessing agreement of data that might be present in more than one data field (e.g. repair of a tear would only be recorded in women who had an OASI; or women who delivered vaginally could not have an onset of labour recorded as pre-labour caesarean). Any implausible distributions or high levels of internal inconsistency would highlight data extraction errors or systematic errors in coding, which would need to be discussed with the unit’s MIS team, and a new revised extract will be requested if required.

#### Data analysis

In stepped-wedge designs, power calculations need to take into account both the clustered nature of the design and the confounding effect of time [30]. The statistical power for the study was calculated using the “steppedwedge” command in STATA 14 [31]. The “steppedwedge” command, written by Hemming and Girling [32] and based on the approach proposed by Hussey and Hughes [33], allows for power and detectable-difference calculations for binary outcomes, following the specification of the number of clusters (units) at each step, the number of steps, the average cluster (unit) size, and the intra-cluster correlation coefficient (ICC, rho). In this study, the number of steps and the number of units per step are both four, totalling 16 units. Unit sizes (the number of vaginal deliveries in each participating unit) were available from national maternity statistics data for each country [28, 34, 35]. There were on average 304 vaginal births a month for each participating unit (with a range of 113–539) in 2014/2015, therefore the average cluster size was 912 vaginal deliveries per unit in a three-month period (duration of each step). The baseline OASI rate and the intra-cluster correlation (ICC, rho) were calculated from English maternity clinical indicators data for 2013/14 [36]. For the 13 participating English units, the OASI rate for all vaginal deliveries was 3.2% and the ICC was 0.0062 (CI:0.0018 to 0.0214). The statistical power of the study to detect a 25% reduction in OASI rate (from 3.2 to 2.4%) is 0.92. Under various scenarios (e.g. using lower confidence interval value for ICC, a cluster size of 700 or a baseline OASI rate of 2.8%), the statistical power remains over 80%.

In stepped-wedge studies, the proportion of units exposed to the intervention gradually increases, meaning that unexposed observations will, on average, be from an earlier calendar time than exposed observations [30]. Furthermore, improved reporting and increased awareness of the care bundle over the period is likely to have an impact on the OASI rates [1]. Thus, calendar time is associated with both the exposure to the intervention and also the outcome, and is therefore a potential confounder. We will use logistic mixed effects regression to model the log odds of sustaining an OASI, with a fixed effect for each step and a random effect to account for clustering at the unit level [33, 37]. The model will include a linear secular trend and also adjust for risk factors for OASI (maternal age, BMI, ethnicity, mode of delivery, episiotomy, birthweight, prolonged labour, and shoulder dystocia) [1].

Additional analyses are planned subject to completeness and quality of data collected for monitoring purposes throughout the study, including data on care bundle compliance, either on a paper form or electronically. In addition, these summary measures of organisational readiness and trends in the uptake of the intervention (i.e. percentage of clinicians trained and compliance rate) may also be used to explore the impact of these organisational factors on clinical outcomes.

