#### Study setting

To ensure representation across regions, England, Wales and Scotland were divided into four geographical blocks as follows:Region 1: London, South East Coast, Wessex, Thames ValleyRegion 2: Cheshire and Mersey, South West, West Midlands, WalesRegion 3: East Midlands, East of England, Yorkshire and the HumberRegion 4: Greater Manchester, North, Scotland

The 91 units which had expressed an interest in taking part in the pilot study were used for the selection process for the scale-up. Within each region, four units were selected to obtain a total of sixteen units, aiming for at least one from each of the clinical senates in the region, at least one from each of the four maternity unit size categories (defined by the National and Perinatal Audit as < 2500, 2500–3999, 4000–5999 and 6000+ births per year [25]) and at least one from each of the three types of maternity units; namely obstetric-led (hospital based care where obstetricians take responsibility for high-risk women and midwives take responsibility for low-risk women), alongside midwifery units (where midwives provide care for low-risk women in co-located units in the same building as an obstetric unit) and freestanding midwifery unit (often called ‘birth centres’, these are geographically separate from obstetric units and midwives provide care for low-risk women) [26]. A list of the sixteen study units can be found on the ISRCTN database.

All vaginal births are potentially eligible for the intervention when the attending clinician (midwife or obstetrician) has been trained to use the care bundle. Women are excluded if they are in a birthing position that makes it impossible to implement all aspects of the care bundle (e.g. water birth). Given an average number of 304 deliveries per month in each unit, a target of 70% of clinicians having been trained (i.e. deliveries being eligible) and the assumption of up to 10% vaginal deliveries being excluded due to birthing positions, the estimated number of women potentially eligible to receive the care bundle intervention is 32,800 (Table 1).

**Table 1 Tab1:** Design of the stepped wedge trial for OASI Care Bundle evaluation

Region	Time					
	0	1	2	3	4	5
1		Roll-out	3280	3280	3280	3280
2			Roll-out	3280	3280	3280
3				Roll-out	3280	3280
4					Roll-out	3280

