## Methods

The study has a stepped-wedge design with complete, continuous recruitment [27]. In stepped-wedge designs, the short-exposure intervention is implemented at the healthcare provider level and staggered in blocks.

The four regions were sequentially randomised to the intervention, using a random number generator. The first region was initiated in January 2017, and the intervention was introduced to remaining regions every three months. The units were informed of their allocation two months before the start of their roll-out period in order to allow for preparation time. The first three months of the intervention is the ‘transition phase’, which is when the care bundle launched at the units, and the local champions cascade the skills development module to their colleagues.

Mixed methods will be used to assess the clinical effectiveness and the implementation outcomes of the OASI Care Bundle. Clinical outcomes will be assessed via routinely collected patient-level data, captured through each unit’s Maternity Information System (MIS). Implementation outcomes will be assessed through specific qualitative and quantitative methods, which will provide a detailed evaluation of the acceptability, feasibility, coverage and sustainability of the intervention.

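### The stated power of 0.92 fits a five-period wedge with no transition phase; the six-period design with a roll-out period gives about 0.73 to 0.83 unless roll-out births count wholly as one condition

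*Protocol article*

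**What the plan says.** The power paragraph under Data analysis lists its inputs. On the layout: "the number of steps and the number of units per step are both four, totalling 16 units". On size: "the average cluster size was 912 vaginal deliveries per unit in a three-month period (duration of each step". The baseline rate is 3.2% and the ICC 0.0062 (interval 0.0018 to 0.0214). No transition period is listed. The result is "The statistical power of the study to detect a 25% reduction in OASI rate (from 3.2 to 2.4%) is 0.92". The next sentence varies the ICC, the cluster size and the baseline rate, and ends "a cluster size of 700 or a baseline OASI rate of 2.8%), the statistical power remains over 80" per cent.

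The design is set out elsewhere. Table 1 ("Design of the stepped wedge trial for OASI Care Bundle evaluation") has times 0 to 5, and each region has a roll-out cell before its first counted intervention cell. The Methods section makes the first three months of each region's intervention a transition phase, "which is when the care bundle launched at the units, and the local champions cascade the skills development module to their colleagues". The Data source section describes an 18-month extract with baseline, transition and implementation phases. It also adopts the principle that "primary analyses need to be based mainly on data from those exposed to the intervention or control while clusters are in both conditions".

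**The concern.** The power inputs describe a wedge with one control period, four steps and no gap between control and intervention, which makes five periods. The design as drawn has six periods and a three-month buffer per region, when some clinicians are trained and others are not. Births in that buffer are neither clean control nor clean intervention.

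If the buffer is set aside, times 0 and 1 contain only control births and times 4 and 5 only intervention births. Only times 2 and 3 contain both conditions, and that within-period contrast carries most of the information once time is adjusted for. A reader who takes 0.92 at face value puts the false-negative risk at 8%, and below 20% in the less favourable scenarios. If the true risk is two to three times as large, a null result would carry less weight than the article suggests.

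**Working it through.** **Inputs** (Data analysis section): 16 units, 4 per step; m = 912 births per unit per period; p1 = 0.032, p2 = 0.024, difference 0.008; ICC ρ = 0.0062. Assumed: two-sided alpha of 5%. The variance convention is not stated either, so each range runs from variance at the baseline rate (3.2%) to variance at the mean rate (2.8%).

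**Step 1: reproduce 0.92 with five periods and no transition.** In the Hussey-Hughes model with I units and T periods,

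Var = Iσ²(σ² + Tτ²) / [(IU − W)σ² + (U² + ITU − TW − IV)τ²]

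- Total variance: 0.032 × 0.968 = 0.030976.
- τ² = 0.0062 × 0.030976 = 0.00019205.
- σ² = 0.9938 × 0.030976 / 912 = 0.00003375.
- U (exposed unit-periods) = 4 × (4+3+2+1) = 40.
- W (squared period totals) = 0 + 16 + 64 + 144 + 256 = 480.
- V (squared unit totals) = 4 × (16+9+4+1) = 120.
- IU − W = 640 − 480 = 160.
- U² + ITU − TW − IV = 1600 + 3200 − 2400 − 1920 = 480.
- Var = 5.50 × 10⁻⁶, so SE = 0.00235.
- Power = Φ(0.008/SE − 1.96) = Φ(1.45) = 0.927.

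Mean-rate variance gives 0.953. The article's scenarios on this layout give 0.94–0.96 (ICC 0.0018), 0.85–0.89 (m = 700) and 0.89–0.925 (baseline 2.8%, keeping the 25% reduction, so 2.1%). All exceed 80%, so both power statements match this design.

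**Step 2: six periods with roll-out cells omitted.** With empty cells the same model needs the general form: Var is the treatment entry of (Σ Xᵢ′Vᵢ⁻¹Xᵢ)⁻¹, where Vᵢ has σ² + τ² on the diagonal and τ² elsewhere. With period effects and baseline-rate variance, SE = 0.00311 and power = Φ(0.008/0.00311 − 1.96) = 0.73. Mean-rate variance gives 0.78. The variance is (0.00311/0.00235)² = 1.75 times that of Step 1.

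**Step 3: other ways to keep roll-out apart.** The Data analysis section names both a fixed effect for each step and a linear trend, so both forms of time were run.

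| Roll-out births, time | Base case | m = 700 | Baseline 2.8% | ICC 0.0018 |
|---|---|---|---|---|
| Excluded, period effects | 0.73–0.78 | 0.62–0.68 | 0.67–0.73 | 0.75–0.80 |
| Excluded, linear trend | 0.77–0.82 | 0.66–0.72 | 0.71–0.77 | 0.79–0.84 |
| Own term, period effects | 0.76–0.81 | 0.65–0.71 | 0.70–0.76 | 0.78–0.83 |
| Own term, linear trend | 0.78–0.83 | 0.67–0.72 | 0.72–0.77 | 0.80–0.85 |

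**Step 4: roll-out births coded as fully exposed** (period effects). The result depends on how much of the effect is present during roll-out. The article does not give this share, so a range is shown.

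| Share of effect during roll-out (assumed) | Power |
|---|---|
| 50% | 0.51–0.57 |
| 70% | 0.75–0.80 |
| 80% | 0.84–0.88 |
| 90% | 0.90–0.94 |
| 100% | 0.95–0.97 |

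At 50% the estimate also shrinks to 56% of the true effect. Coding roll-out births as control is the mirror image: 0.95–0.97 if no effect is present during roll-out, 0.80–0.84 if a quarter of it is.

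**The case against.** The strongest objection is that the article never excludes roll-out births. A reader might infer exclusion from the missing counts in Table 1, but the control cells have no counts either. The table counts women eligible for the bundle (10 cells × 3280 = 32,800), so a cell without a count does not mean a cell left out of the analysis. The Methods section also calls these months part of the intervention, and the extract includes them. This stands: 0.73–0.78 is conditional on exclusion with period effects, and is not the power of a stated analysis.

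Two further readings go too far. One is that counting roll-out births as exposed cannot rescue the figure. It can, if about 90% or more of the effect is present during roll-out. The article gives no share, but it describes those months as the time when training is being passed on, which makes so high a share hard to presume. The other is that all three robustness scenarios fail. The lower ICC limit does not clearly fail, since its range straddles 80%.

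It can also be said that the handling of transition births belongs in the analysis plan. That is fair for the modelling detail. It does not cover a printed power figure whose listed inputs match a different layout from the article's own table.

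**Conclusion.** The concern holds in conditional form. The figure 0.92 matches a complete five-period wedge and takes no account of the roll-out period in the design described. Where roll-out births are kept apart from both conditions, power for 3.2% to 2.4% is about 0.73–0.83, a false-negative risk of roughly 17–27% against the implied 8%. In all those variants the claim of over 80% fails for 700 births per period and for a 2.8% baseline. Among the codings examined, power near 0.92 returns only if roll-out births are assigned wholly to one condition and behave almost entirely like it.

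This rests on a two-sided 5% test, the normal approximation, a random unit intercept with constant ICC, equal unit sizes of 912, and the two variance conventions shown. The convention that reproduces 0.92 gives the lower end of every range.

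**What to change.** State how roll-out births enter the primary model: excluded, or kept with their own exposure term, rather than counted as full intervention or full control. Recompute power from the six-period layout for that choice and for the form of time adjustment intended, giving the alpha and variance convention used. With period effects, 0.92 would become about 0.73–0.78 if roll-out births are excluded, or about 0.76–0.81 with their own term. Replace the scenario sentence with the matching figures, since over 80% cannot stand for the smaller cluster size or the lower baseline rate.

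The cost is one recalculation, a few changed sentences and a less favourable stated power. No extra units, births or data are needed. The own-term option uses births already in the extract and recovers about three percentage points of power over exclusion when period effects are used.

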## Abstract

**Background:**

Third and fourth degree perineal tears, or obstetric anal sphincter injuries (OASI), sustained during childbirth can result in anal incontinence and psychosocial problems which require ongoing treatment. Within the English National Health System (NHS) reported rates of OASI have gradually increased. In response, a care bundle was developed incorporating four elements: 1) antenatal information to women, 2) manual perineal protection during all vaginal births, 3) episiotomy to be performed with a 60° mediolateral angle at crowning (when clinically indicated) and 4) perineal examination (including per rectum) after childbirth. Implementation of the OASI Care Bundle is aided by a skills development module and an awareness campaign. The project is a collaboration between two national professional bodies, an NHS hospital trust and an academic institution.

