**Methods:**

Implementation of the OASI Care Bundle will be evaluated using a stepped-wedge design. From January 2017 sixteen maternity units across England, Wales and Scotland will participate in the study over a 15-month period, with sequential roll-out of the intervention in four blocks (regions) of four units. The primary clinical outcome is OASI rate. Regression analysis will adjust for differences in organisational characteristics and obstetric risk factors in women who gave birth before and after implementation of the care bundle. Focus group discussions and in-depth interviews with clinicians will evaluate the feasibility of integrating the care bundle into routine practice. Interviews with women will explore the acceptability of the intervention.

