**Fig. 1 Fig1:**
[figure not shown]
Development of the OASI Care Bundle. This shows the stepwise development of the care bundle which began with the summit of national experts and the formation of a working group (the OASI Care Bundle group) in May 2014

The results of the review and recommendations from pre-existing UK guidelines [9, 23] were presented to the OASI Care Bundle group, comprising of clinical and methodological experts with representatives from the RCOG, RCM and the London School of Hygiene and Tropical Medicine (LSHTM). This led to a structured discussion about the clinical practicalities of each individual care bundle element. The four elements finally included by the OASI Care Bundle group were:Women to be given information during the antenatal period about perineal trauma and how to minimise their risk of sustaining an OASI.When clinically indicated, a mediolateral episiotomy should be performed at a 60-degree angle to the midline at crowning.Documented use of Manual Perineal Protection (MPP) for:All spontaneous vaginal births, unless the woman’s chosen birth position does not allow for it (e.g. water birth)All instrumental vaginal births (e.g. forceps, ventouse and kiwi)Following birth, the perineum should be examined and any tears graded in accordance to RCOG guidelines [9]. The examination should include a per rectum check, even if the perineum appears intact.

Following presentations to the RCM and other leaders of labour care and birth, changes were made to the care bundle manual and the training materials to emphasise support for women’s birth choices, the importance of mobility during labour and natural birth physiology.

In January 2015, a survey was sent to all UK maternity units to assess their interest in piloting the OASI Care Bundle. From the 91 units who responded, two were chosen to carry out a three month pilot study. The main aim of the pilot was to determine whether the care bundle was acceptable and feasible for clinicians. Following the pilot study, funding was obtained from the Health Foundation to adapt and scale-up the OASI Care Bundle as a quality improvement project, to be implemented in sixteen maternity units across England, Wales and Scotland; this forms the current project.

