#### Monitoring of clinical data during implementation of the OASI care bundle

Clinical data will be monitored on a weekly basis by the evaluation team. These data include rates of OASI, episiotomy and caesarean sections, as well as the number of eligible and care bundle compliant births. In addition to providing information on coverage, routine monitoring of data may be used to trigger additional Project Team communication or support if an unusual clinical activity is observed. Additionally, evidence of integration of the care bundle into routine practice will be continuously monitored by assessing the number of eligible and care bundle compliant births each week. Statistical process control techniques will identify any unusual patterns in OASI or compliance rates.

Each unit will be sent a six month summary of their OASI rates and compliance data. In order to facilitate shared learning, this six month summary will also be aggregated by region (with anonymization of data) and be provided to the four units within that region. This is a quality improvement project which aims to reduce rates of OASI. With this in mind, a critical review after six months, with sharing of anonymised results amongst neighbouring units, will facilitate learning for all units in order to understand what has gone well and which areas need to be targeted to further accelerate any change in OASI rates. Similar summaries (to individual units and at regional level) will be provided at nine months and twelve months. Provision of such feedback contributes to the ‘Communications and Awareness Campaign’ component of the ‘Theory of Change’ and will provide information about the effectiveness of the care bundle. Such information will promote engagement with the care bundle and help enable change.

Fidelity is seen as a crucial factor to determine whether the care bundle is implemented as it is intended. However, as the care bundle is implemented at time of birth, it is not possible in practice for an impartial observer to monitor whether each care bundle component is correctly carried out for each birth. Where possible, the Project Team advocates the presence of a second midwife at birth who can observe practice and help identify any training needs. Additionally, the awareness campaign, continued skills development, presence of the local champions and unit visits by the Project Team will contribute to ensuring that intervention is correctly implemented.

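### The primary model adjusts for episiotomy, a post-exposure bundle element; if the bundle changes how often or in whom it is done, the odds ratio is not the bundle's total effect

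*Protocol article*

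**What the plan says.** The protocol article's Data analysis section describes one regression model for the primary outcome: "We will use logistic mixed effects regression to model the log odds of sustaining an OASI", with a fixed effect for step, a random effect for unit and a linear secular trend. The same model will "adjust for risk factors for OASI (maternal age, BMI, ethnicity, mode of delivery, episiotomy, birthweight, prolonged labour, and shoulder dystocia".

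Epiotomy's place in the bundle is stated twice. The Abstract lists "episiotomy to be performed with a 60° mediolateral angle at crowning (when clinically indicated" among the four elements. The section on development of the care bundle says "When clinically indicated, a mediolateral episiotomy should be performed at a 60-degree angle to the midline at crowning".

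The Data source section classes it as "intrapartum care (e.g. episiotomy, induction of labour, epidural use, shoulder dystocia and mode of birth", that is, care given during labour and birth. No field for angle or timing is named there.

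The Abstract explains what adjustment is for: "Regression analysis will adjust for differences in organisational characteristics and obstetric risk factors in women who gave birth before and after implementation". The section Study design and participants gives the overall aim as lowering OASI rates.

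**The concern.** In a stepped-wedge evaluation the exposure is the unit's switch to the bundle. Whether a woman then has an episiotomy is settled afterwards, by a clinician whose practice the bundle addresses. It is not a feature of the women that differs by chance or calendar time, which is what the Abstract says adjustment is meant to handle.

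Conditioning on it can do two things. It can block the route from bundle to episiotomy practice to OASI. Because episiotomy is done on indication, it can also link the bundle to unmeasured reasons for the episiotomy, such as a difficult birth. Both require that the bundle alters how often, or in whom, episiotomy is done. If it does, the primary odds ratio would be reported as the effect of implementing the whole bundle while estimating something else.

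**Working it through.** **1. The plan's own figure.** Inputs from Data analysis: 16 units, 4 steps, 912 births per unit per three-month period, OASI 3.2% falling to 2.4%, ICC 0.0062. Assumed: 5 periods and two-sided alpha 0.05. The Hussey and Hughes variance, with total variance 0.032 × 0.968, gives a standard error of 0.00235. Then z = 0.008 / 0.00235 = 3.41, and power = Φ(3.41 − 1.96) = 0.927, against 0.92 stated. The figure reproduces; the concern does not rest on it. The target odds ratio is (0.024/0.976) / (0.032/0.968) = 0.744.

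**2. Share of the target carried by a change in rate.** The protocol gives no episiotomy rate and no episiotomy effect, so these inputs are assumptions. With rate e0 before and e1 after, and relative risk RR of OASI with episiotomy:

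relative reduction through the rate = 1 − [(1 − e1) + e1·RR] / [(1 − e0) + e0·RR]

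| e0 → e1 | RR | Ratio | Reduction | Share of the 25% target |
|---|---|---|---|---|
| 20% → 25% | 0.8 | 0.95 / 0.96 | 1.0% | 4% |
| 20% → 30% | 0.8 | 0.94 / 0.96 | 2.1% | 8% |
| 20% → 25% | 0.6 | 0.90 / 0.92 | 2.2% | 9% |
| 20% → 30% | 0.6 | 0.88 / 0.92 | 4.3% | 17% |

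**3. The same question on the odds-ratio scale.** Hold the total effect at 3.2% to 2.4% (odds ratio 0.744) and the control rate at 20%. Let episiotomy carry an odds ratio for OASI of 0.3 to 0.7, a wider assumed range than in step 2. Solve for the bundle odds ratio conditional on episiotomy. The last column is the power of the design in step 1 if that odds ratio is what is estimated.

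| Rate under the bundle | Adjusted odds ratio | Change in log odds ratio | Power |
|---|---|---|---|
| 15% | 0.714–0.732 | overstated by 5–14% | 0.95–0.97 |
| 20% (unchanged) | 0.743–0.744 | essentially none | 0.93 |
| 25% | 0.756–0.775 | 5–14% removed | 0.85–0.90 |
| 30% | 0.768–0.810 | 11–29% removed | 0.71–0.87 |

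**4. Technique changes, rate does not.** Assume a bundle odds ratio of 0.8 for all women, an episiotomy rate of 20% throughout, and an episiotomy odds ratio that improves from 0.7 to 0.35 because angle and timing improve. The odds ratio for the bundle is 0.739 without episiotomy in the model and 0.739 with it. A yes/no covariate leaves the benefit of better technique in the bundle coefficient.

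Steps 2 to 4 do not include bias from unmeasured indications, which was not quantified.

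**The case against.** The strongest reply is that the bundle element concerns how an episiotomy is done when it is indicated. It does not tell units to do more or fewer. A reader might infer that the primary odds ratio describes the bundle apart from its episiotomy element. The documents do not support that: step 4 shows that the effect of technique stays in the coefficient. This limit stands, and the concern is conditional on a change in frequency or selection.

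A reader might also infer that the sponsor expects the rate to change, because of the weekly monitoring: "These data include rates of OASI, episiotomy and caesarean sections, as well as the number of eligible and care bundle compliant births". Caesarean section, which is not a bundle element, is watched in the same way, and the stated use is to respond to unusual activity. This is surveillance. It shows at most that a change was thought possible.

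The bias through indication is partly handled, since the model also contains mode of delivery, prolonged labour, shoulder dystocia and birthweight. Unmeasured indications would remain.

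It would be tempting to strip out every intrapartum covariate. The case for that is weaker. Those covariates are not bundle elements, the Background names instrumental birth and prolonged second stage as OASI risk factors, and with only four regions randomised, adjustment for strong risk factors has value.

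Finally, an analysis plan that is not shown may hold a companion model without episiotomy. Its absence here is not held against the article. The point is the covariate that the article does fix.

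**Conclusion.** The concern holds in conditional form. The protocol places a post-exposure bundle element in the covariate list of the primary model, although its aim and its stated reason for adjustment call for the total effect of implementing the bundle, adjusted for differences between the women. If the bundle changes how often or in whom episiotomy is done, the adjusted odds ratio is not that total effect. If the frequency and selection stay the same, almost nothing is lost.

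The size cannot be computed from the documents. Under the assumptions in step 2 it is about 4–17% of the planned 25% reduction. The wider assumptions in step 3 reach 29% of the log odds ratio at their extreme, and a falling rate reverses the sign. Because the size may be nil and its direction is unknown, this is a should-fix. It still merits correction, because whether the condition will arise cannot be known when the model is fixed.

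**What to change.** Remove episiotomy from the covariate list of the primary model and leave the other listed covariates as they are. Report the episiotomy rate before and after implementation as a process outcome. Present the episiotomy-adjusted model only as a secondary analysis, labelled as not estimating the total effect of the bundle.

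The cost is one change to the covariate list and two short additions to the reporting. Episiotomy is already in the data specification, so no new data are needed, and the stated sample size and power do not change. Dropping the covariate costs at most a little precision.
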